### Trial governance

Sunderland Research Ethics Committee (REC) has given the SamExo pilot trial a favourable ethical opinion (reference 10/H0904/57). The Newcastle upon Tyne NHS Hospitals Foundation Trust is acting as the trial sponsor. A Trial Management Group is overseeing the overall conduct and progress of the study and provides day-to-day support to collaborating sites. Training has been given to collaborators through investigator meetings, site initiation visits and routine monitoring visits. Quality control is maintained through adherence to the study protocol, Standard Operating Procedures (SOPs), principles of good clinical practice, research governance and clinical trial regulations. As agreed by the sponsor a Trial Steering Committee (TSC), which includes a parent representative, is adopting the joint roles of TSC and Data Monitoring & Ethics Committee (DMEC), with independent members meeting in closed session to fulfil the DMEC role.

### Potential risks and adverse events

This is a low-risk trial and major safety data are not anticipated. The major identified risk for participants is that those in the active monitoring arm may experience a natural deterioration in their clinical condition. This risk will be managed by 3-monthly assessments of the child for the duration of the study. Children will be offered treatment if there is a significant deterioration, or if the parent wishes to discontinue monitoring in favour of eye muscle surgery and the clinical team agrees that surgery is appropriate following a discussion of the risks and benefits, based on currently available information. Participation may generate anxiety for some parents and children
[39]: this risk will be managed by providing ready access to sources of advice and support (for example the TO). Study information provided to parents and participants includes an account of existing knowledge of the natural history and current management of X(T). Parents are informed that their children will be regularly assessed and encouraged to report concerns about their child’s X(T) to the TO who will take these to the local PI. The latter will arrange for eye muscle surgery if the child meets the usual criteria for surgery. Parents will be encouraged to report concerns about the conduct of the study to the Trial Steering Committee, Sponsor and Funder.

Adverse event reporting following surgery will be undertaken in accordance with the National Research Ethics Service (NRES) guidelines for adverse event reporting in non-CTIMP trials. A serious adverse event (SAE) in this pilot trial is defined as an untoward occurrence that:

• results in death

• is life-threatening

• requires hospitalisation or prolongation of existing hospitalisation

• results in persistent or significant disability or incapacity

• is otherwise considered medically significant by the investigator

Expected adverse events, both common and rare after X(T) surgery, are listed in Table 
2. If a patient experiences an SAE it will be reported to Sunderland REC when, in the opinion of the chief investigator, the event was ‘related’: that is, resulted from administration of any of the research procedures; and ‘unexpected’: that is, the type of event is not listed in the protocol as an expected occurrence. Any SAEs will be reported to the NCTU within 24 h of the PI learning of its occurrence. Reports of related and unexpected SAEs will be submitted to the REC within 15 days of the chief investigator becoming aware of the event, using an NRES ‘report of serious adverse event’ form.

**Table 2 T2:** Expected adverse events during the SamExo pilot trial

**Procedure**	**Adverse event:**	
	**Common & well understood consequences of treatment**	**Rare events**
Perforation of the globe	Occurring within 24 h	Occurring after 24 h
Intraocular infection	Occurring within 2 weeks	Occurring after 2 weeks
Lost or slipped muscle	Occurring within 1 month	Occurring after 1 month
Scleritis	Occurring within 1 month	Occurring after 1 month
Becoming constant XT	Occurring within 9 months	Occurring after 9 months
Persistent over-correction	Occurring within 9 months	Occurring after 9 months
Re-operation for under- or over-correction	Occurring within 9 months	Occurring after 9 months

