[18] (reduced acuity in one eye caused by decreased quality visual input during the critical period of development). Typically, X(T) is first spotted in early childhood by parents noticing that their child’s eye is wandering outward as they look at objects in the distance or when they are very tired, inattentive or in bright sunlight.

Conservative treatment options for X(T) include occlusion with eye patches or wearing glasses that stimulate convergence. Eye muscle surgery can also be performed in order to realign the eyes. However, many clinicians and parents opt for an active monitoring approach, that is, they decide to wait and see whether the squint resolves spontaneously or at the very least does not deteriorate. Long-term natural history data are lacking, but there is some indication from observational work that X(T) surgery is more successful than conservative treatment and active monitoring in improving control of the eyes
[19]. However, the success of surgery is not guaranteed: it comes with a risk of over-correction whereby the eye alignment converts to a constant convergent deviation (esotropia) with a consequent loss of function in terms of stereovision and the potential to develop amblyopia in young children or diplopia (double vision) in older children. Alternatively, an under-correction may occur with persistence of the X(T). There is also evidence that the effectiveness of surgery declines over time
[26]. There is considerable variability in rates of surgery and a lack of consistency in the surgical indications for treatment of X(T) in the UK
[18,19]. Here, the majority of children with the condition do not appear to undergo eye muscle surgery within 2 years of presentation and instead are monitored recurrently, with significant loss to clinical follow-up.

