### Proposed outcome measures

For children with X(T), and their parents, the most relevant outcome from intervention is the restoration of normal eye alignment, with associated cosmetic and functional benefits. The primary outcome in a full-scale trial will therefore be the difference in the cure rate of X(T) between the surgical and actively monitored group; this is also the primary outcome for which data will be collected in the current pilot in order to inform sample size calculations for a definitive RCT. Cure will be defined as:

• a control score (NCS) of 0 (misalignment never noticed by parents, no observable deviation on cover test)

• demonstrable near stereoacuity in children over 3 years of age

Secondary outcomes include age-specific QOL assessments, median scores of control of exotropia assessed by parental report and clinical components of the NCS and the Mayo Score, rates of amblyopia, use of health-care resources, NHS costs, costs to families accessing the treatments being evaluated and incremental cost per cured patient (with cure as defined by the primary outcome), and a cost-consequences analysis based on the incremental cost with respect to changes in all relevant outcomes where possible.

The key outcomes of this pilot study are:

• data on the variability of the primary and secondary outcome measures;

• rates of participant recruitment and randomisation;

• nature and extent of participation bias;

• rates of cross-over and retention of recruited participants;

• nature and extent of biases arising from cross-over or loss to follow-up.

An initial recruitment rate of >60% and a retention rate of >70% will be considered necessary to indicate feasibility of a full-scale RCT.

Our intention in the full trial would be to conduct a cost-effectiveness analysis based on incremental cost per cured patient (as defined by the primary outcome) and a cost-consequences analysis based on incremental cost with respect to changes in all relevant outcomes where possible, including the QOL measure and different clinical measures. In the pilot study, we will rehearse this cost-effectiveness analysis to inform the study hypothesis and the analysis plan for the definitive trial. We will also assess the ease of collecting information on outcome and costs needed for the health economics analysis.

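### Progression to constant exotropia is a listed adverse event after surgery but has no defined counterpart in unoperated children under active monitoring

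*Protocol article*

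**What the plan says.** In the protocol article, under Potential risks and adverse events, the reporting rule begins: "Adverse event reporting following surgery will be undertaken in accordance with the National Research Ethics Service (NRES) guidelines". The expected-event list is introduced in the same terms: "Expected adverse events, both common and rare after X(T) surgery, are listed in Table" 2. That table includes "Becoming constant XT" and "Persistent over-correction", each classed by whether it occurs within or after 9 months, and its column headings speak of consequences of treatment. The table's own title is wider and refers to events during the pilot trial.

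The same section states: "The major identified risk for participants is that those in the active monitoring arm may experience a natural deterioration in their clinical condition". This risk is to be managed by 3-monthly assessments and an offer of treatment. No event is defined for it.

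Under Proposed outcome measures the primary outcome is cure (an NCS of 0, with near stereoacuity in children over 3 years). The secondary list begins "Secondary outcomes include age-specific QOL assessments, median scores of control of exotropia" and goes on to amblyopia rates, resource use and costs. Cross-over and retention rates are key pilot outcomes. Statistical methods plans between-group tests of control scores at baseline and 9 months and amblyopia rates in the two groups. It plans no tabulation of constant exotropia.

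**The concern.** Constant exotropia is not peculiar to surgery. The Background describes it as a way in which the untreated condition may progress, and the Exclusion criteria keep out children who already have it (other than microtropia). Any case during follow-up is therefore new and could arise in either arm. As worded, the same finding is a listed adverse event if it follows an operation and has no event category if it does not. The gap also covers a child allocated to surgery who becomes constant while waiting for the operation.

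The pilot is meant to rehearse procedures and outcome measurement and to inform the design of a full trial. If it runs as worded, it ends without a rate of the event it calls the major risk of one of its two strategies, and the definition has not been tried out in the arm where it matters most. A safety table built on the stated rule could also show constant exotropia under surgery with nothing recorded beside it under monitoring.

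**Working it through.** The plan states no harm rate, so there is no figure to reproduce. The check is whether any other stated measure yields the proportion of each randomised arm that progresses to constant exotropia.

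1. **Cure.** A child with constant exotropia, one with unchanged intermittent exotropia and one who is over-corrected all count as not cured. Progression is not separated.
2. **Control scores (NCS 0 to 9, Mayo 0 to 10, higher is poorer).** These are compared between arms at 9 months, so worsening contributes to the comparison. It is not isolated. In 60 children the median is the mean of the 30th and 31st ordered scores. If three children below the median moved to the top of the scale, the median would become the mean of the former 33rd and 34th scores, a shift of three ranks. A rank test also returns no proportion.
3. **Cross-over.** Surgery may be offered to a monitored child when a constant squint appears to be developing, or at parental request with clinical agreement. The cross-over rate mixes the two. A child who became constant, was operated on and was no longer constant afterwards would leave no trace as a post-surgical event.
4. **Amblyopia.** This is determined in both groups at 3, 6 and 9 months, but it is one possible consequence of progression, not progression itself.
5. **Serious adverse events.** These rules cover any patient. Constant exotropia in a monitored child would enter only if it met the disability criterion or the investigator judged it medically significant, so capture depends on case-by-case judgement.

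No stated measure gives the rate.

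**What the pilot could estimate.** Inputs: 120 children retained at 9 months (Abstract) and 1:1 allocation (Randomisation), so n = 120/2 = 60 per arm. Event counts are illustrative. The Wilson 95% limits, with z = 1.96 and z² = 3.8415, are

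[p + z²/(2n) ± z√(p(1−p)/n + z²/(4n²))] / (1 + z²/n)

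- 0/60: lower limit 0; upper limit z²/(n + z²) = 3.8415/63.8415 = 6.0%. The exact limit 1 − 0.025^(1/60) is also 6.0%.
- 3/60: centre (0.0500 + 0.0320)/1.0640 = 0.0771; half-width 1.96 × √(0.000792 + 0.000267)/1.0640 = 0.0599; interval 1.7% to 13.7%.

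**Why description and not a test.** Power at two-sided 5% is Φ{[|p₁−p₂| − 1.96√(2p̄(1−p̄)/n)] / √(p₁(1−p₁)/n + p₂(1−p₂)/n)}. The rates below are assumptions, since the document gives none.

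| Assumed rates | Power, 60 per arm |
|---|---|
| 2% vs 8% | 32% |
| 2% vs 10% | 45% |
| 5% vs 15% | 45% |
| 5% vs 20% | 70% |

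For 2% vs 8%: (0.0600 − 1.96 × 0.0398)/0.0394 = −0.46, and Φ(−0.46) = 32%.

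**The case against.** The strongest case against has four parts.

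**Capture is wider than the one sentence suggests.** A reader might infer that adverse events are collected only after surgery and that no outcome reflects either harm. The article does not support that. Serious adverse events are reportable for any patient, Table 2's title is not limited to surgery, and amblyopia and control scores cover both arms. This stands, but none of it supplies a rate of constant exotropia.

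**Over-correction is already covered.** It follows an operation, it is in Table 2 together with re-operation, and the rule reaches every operated child, including a monitored child who crosses over. This stands in full: limiting that event to operated children creates no imbalance in ascertainment.

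**No harm comparison is planned, so none is biased.** It is tempting to say that the pilot's harm comparison is tilted against surgery, or that the pilot fails its aim of weighing risks against benefits. The article plans no formal comparison of these harms. Weighing risks and benefits is its ultimate goal for a full trial, whereas the pilot's four objectives concern recruitment, adherence and follow-up, reasons for participation, and procedures. The sample size text also disclaims power. What remains is the narrower risk that a table built on the stated rule would be lopsided.

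**This is a condensed article.** Non-serious event recording and safety tables may be set out in the full protocol, the operating procedures or an analysis plan. That lowers the weight of the point. It does not remove it, because the article states a rule tied to surgery; it does not merely omit detail.

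**Conclusion.** The point holds as an asymmetric definition. Constant exotropia is a named adverse event for operated children and has no defined event for unoperated ones, although deterioration under monitoring is called the major risk. No listed outcome gives its rate by randomised arm.

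The weight is modest: the pilot's feasibility conclusions on recruitment and retention are unaffected. What is lost is a descriptive estimate with an upper limit of about 6% if no events occur, or an interval of about 1.7% to 13.7% at three events. These figures assume 60 per arm. Trial status reports that fewer patients were eligible and fewer agreed than predicted, so the real intervals may be wider.

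**What to change.** Reconcile Proposed outcome measures, Statistical methods, Potential risks and adverse events, and Table 2 as follows.

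- **Constant exotropia:** state one definition and apply it to all randomised children at the 3-, 6- and 9-month visits. Count any occurrence up to 9 months, including before planned or cross-over surgery. Show cross-over numbers beside it, since surgery may be performed before a squint becomes constant.
- **Loss of near stereopsis:** tabulate it among children in whom it was documented at entry, and give the denominator. Entry documentation is required from age 3, and the visit schedule allows either stereovision or motor fusion testing, so not every child will contribute.
- **Persistent over-correction:** state one definition and tabulate it among operated children, by randomised arm.
- **Reporting:** number, proportion and 95% confidence interval by randomised arm, with no formal test. Reword the reporting sentence and the introduction to Table 2 so that constant exotropia is not tied to surgery.

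The cost is wording, a few derived variables and slightly longer safety tables, because alignment, control and binocular function are already assessed at every visit. One limitation should be stated: the 3- and 6-month assessments are made by the unmasked treatment orthoptist, so the masked 9-month finding should also be shown separately. No rule on when to offer or perform surgery changes.

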## Discussion

The optimum management of X(T) in children is contentious, with some clinicians recommending early surgery, some preferring to delay and others choosing to actively monitor. The lack of robust evidence to guide management and the poorly understood natural history of this condition renders it difficult for clinicians to offer clear advice to parents. Consequently, many children are observed without any treatment for extended periods because of the uncertainty surrounding the best course of action. The need for evidence from randomised studies has been acknowledged for some time now
[27], and this is the first attempt, as far as we are aware, to explore the potential for a RCT of surgery versus active monitoring in childhood X(T). We felt it would be inappropriate to undertake a full-scale study involving large numbers of participants and centres before first conducting a feasibility study. The SamExo pilot study will provide important pointers regarding how acceptable a RCT of immediate surgery versus deferred surgery/active monitoring will be to participants and clinicians.

The recruitment phase will give us a good indication of the proportion of eligible children/parents who would sign up to a full trial, the likelihood of them withdrawing from it and also an idea of how many we would need to approach over a given duration to achieve a specified sample size.

Equally pivotal will be the reasons why parents agree or decline the pilot trial, their perceptions of the need for and purpose of randomisation, their views on the nature of the information they received, and suggestions for improving future trials and refining the research question. Findings from these qualitative interviews will not only inform the design of a possible full trial but may also help investigators planning studies of surgical interventions, trials of other children’s eye conditions or paediatric trials in general.

Potential ethical issues include the fact that some of the children in the SamExo pilot study will be asked to wait up to 9 months before being offered surgery. We feel that this can be justified as our previous work has shown that less than 8% of children with X(T) had surgery within the first year following initial assessment when treated in a routine setting
[18]; in some centres, no children had surgery within 2 years of diagnosis
[19]. Children who have very mild X(T) are not being entered into the trial, even though our earlier research found that some of these children did have surgery. Similarly, we are not recruiting children who appear to be at imminent risk of developing a constant squint. Children who are in the active monitoring arm are being regularly assessed and will be offered treatment if they develop, or seem to be at risk of developing, a constant squint. With increased rates of surgery, we may see increased rates of re-operations, persistent over-correction and other surgical complications.

## Trial status

Recruitment to the SamExo pilot trial commenced in September 2011 and is ongoing at the time of manuscript submission. Recruitment was originally scheduled to end in February 2012 but we have extended this phase up to 31 May 2012. (The total duration of the trial is unchanged.) This extension to recruitment was recommended by the TSC in January 2012 and agreed upon by the funders in light of early indications that fewer screened patients were actually eligible for the study and fewer eligible patients had thus far agreed to participate than was predicted.

## Abbreviations

BSV: Binocular stereovision; DMEC: Data Monitoring & Ethics Committee; HSUQ: health services use questionnaire; IOXT: The Improving Outcomes in Intermittent Exotropia study; IXTQ: Intermittent Exotropia Questionnaire; NCS: Newcastle Control Score; NCTU: Newcastle Clinical Trials Unit; NRES: National Research Ethics Service; PI: principal investigator; QOL: quality of life; REC: research ethics committee; RO: research orthoptist; SAE: serious adverse event; SamExo: The Surgery against Active Monitoring in Intermittent Exotropia pilot trial; TO: treatment orthoptist; TSC: trial steering committee; TTQ: time and travel questionnaire; VA: visual acuity; X(T): intermittent exotropia.
